## Methods/design

### Study design

INFORM2 NivEnt is an exploratory non-randomized, open-label, multinational and multicenter seamless phase I/II trial of nivolumab and entinostat in children and adolescents with relapsed / refractory or progressive high-risk solid tumors and CNS tumors. A schematic overview of the trial is provided in Fig. 1. Since the age spectrum comprises a broad range of physical development of the study patients, phase I is divided in 2 age cohorts: 12–21 years and 6–11 years (in the absence of a pediatric liquid formulation for entinostat, no patients younger than 6 years can be enrolled). Although one could argue that for adolescents no dose escalation is necessary since there is no biological reason to expect another RP2D [34], it was decided to include a dose escalation for adolescents since the available adult data is still immature. The separate dose escalations for children 6–11-year-old and adolescents 12–21-year-old was included to fulfill regulatory requirements. The two age cohorts will run independently and follow a 3 + 3 design with two dose levels [35]. With only two dose levels, a model-based phase I design such as the Continual Reassessment Method was considered but would not offer any advantage to the traditional 3 + 3 design. RP2D is the dose at which up to 1 of 6 patients experiences dose limiting toxicity (DLT). Assuming more similarity with adult data, the trial will start with the older age cohort. The younger age cohort starts if either of the following events occur: 0 of 3 patients of the older age cohort experience a DLT in the DLT observation period OR a maximum of 1 of 6 patients of the older age cohort experience a DLT in the DLT observation period. Patients entering the trial on RP2D can seamlessly enter phase II. In order to maximize the chance of detecting early signs of activity of the combination treatment, phase II consists of a biomarker defined four group (A - D) phase II basket trial. If patients harbor more than one biomarker fitting group A, B or C, they will be allocated according the following priority: A: highest, B: intermediate and C: lowest priority. The aim is to identify the biomarker cohorts in which the combination treatment shows promising activity, i.e. a response rate exceeding the historical response rate of p_0_ = 12% which was observed in a comparable pediatric patient population treated in phase I/II trials [3]. A response rate of p_1_ = 30% would be considered as the target response rate to be detected with high probability.

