#### Primary end point phase II (outcomes)

Best response (CR or PR) will be based on Response assessment in neuro-oncology (RANO) criteria for all primary CNS tumors and Response evaluation criteria in solid tumors (RECIST) for non-CNS tumors, defined for each patient as the best response under study combination therapy during the first 6 cycles (assessment every 2 cycles) by central review. The proportion of responders will be reported as response rate.

Calcified or intra-osseous (osteo) sarcoma target lesions which were progressive before initiation of treatment and show SD on response evaluation (confirmation through a subsequent scan at least 4 weeks later) will be considered as a responder.

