#### Secondary end points (outcomes)

Duration of Response (DOR).Disease Control Rate (DCR).Stable disease (SD).Progression-free survival (PFS).Time to Response (TTR).Overall Survival (OS).Immune related Response Rate (RR) measured by immune-related RECIST (iRECIST) criteria and immunotherapy RANO (iRANO) criteria by central review.Entinostat plasma PK.

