### Assessments and collection of outcomes

An overview about diagnostic and therapeutic measures, timing of disease assessment, and study visits is displayed in Additional file 4. In brief, routine visits are planned weekly during the first 2 cycles and every 2 weeks thereafter. Response assessments are scheduled every 8 weeks.

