#### Secondary outcomes

(Confirmed immune-related) response will be evaluated separately for CR and PR, and SD and DCR will be evaluated in addition, also using iRECIST and iRANO. DOR will be evaluated for all patients who experienced (confirmed immune-related) response. Starting time point will be the time when best response was determined. The event-time endpoints PFS, OS and TTR will be estimated using the Kaplan-Meier method, considering all the patients who started the treatment, whatever their compliance to treatment, including if the treatment was stopped prematurely for a reason other than disease progression. 95%-confidence intervals will be provided for the Kaplan-Meier estimates.

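### Kaplan-Meier for time to response in all treated patients overstates the probability of responding under ordinary censoring; use cumulative incidence instead

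*Protocol article*

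**What the plan says.** The protocol article lists TTR among its secondary end points. Statistical methods, Secondary outcomes, fixes the estimator and the analysis set in one sentence: "The event-time endpoints PFS, OS and TTR will be estimated using the Kaplan-Meier method, considering all the patients who started the treatment". Patients stay in the analysis whatever their compliance, "including if the treatment was stopped prematurely for a reason other than disease progression". On precision it adds that "95%-confidence intervals will be provided for the Kaplan-Meier estimates".

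Duration of response is handled differently in the same section: "DOR will be evaluated for all patients who experienced (confirmed immune-related) response". So one response-time endpoint is limited to responders and TTR is not.

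The section gives no rule for when a patient who progresses or dies without responding is censored for TTR, and it names no competing-risk method.

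The primary end point is the "best response under study combination therapy during the first 6 cycles (assessment every 2 cycles) by central review". Elsewhere the article confirms the interval: "Response assessments are scheduled every 8 weeks".

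**The concern.** Kaplan-Meier recognises two states, event and censored. It estimates the event probability correctly only if censored patients would have had the event later at the same rate as those still at risk. For TTR, a patient who has died cannot respond. On the primary definition, which counts response only under the combination and within six cycles, neither can a patient who has stopped treatment. Censoring these patients when they leave redistributes their weight to those still at risk, as if some of them were yet to respond.

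Such patients will be numerous. The article cites survival below 20% after recurrence, a historical response rate of 12% and a target of 30%. Even on target, 70% of patients would not respond.

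At stake is the meaning of the TTR curve. Under ordinary censoring it would rise above the proportion of the same patients who responded, its 95% limits would surround the inflated quantity, and the trial report would carry two conflicting impressions of response.

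**Working it through.** **The plan's own figures.** The article states no figure for TTR. To check the reading of its response rates, the design figures were reproduced. With the stated Beta priors and cut-offs, futility at 10 patients means no responders. The stopping probability is 0.88^10 = 27.85% at a 12% response rate and 0.70^10 = 2.82% at 30% (stated: 27.8% and 2.8%). For cohort D with n = 29 and looks at 10 and 20, type 1 error is 5.02% and power 80.25% (stated: 5.0% and 80.3%).

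**Inputs for TTR.**
- From the article: three assessments 8 weeks apart (six cycles, one assessment every two cycles); true response probabilities 12% and 30%.
- Assumed, because the article gives no value: a fraction c of non-responders progresses or dies per 8-week interval, from 0.1 to 0.7.

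**Formulas.** Let h be the probability of first response at a scan among those at risk, and q = (1-h)(1-c).
- True cumulative response = h(1 + q + q²).
- 1-KM, with progression and death censored when they occur = 1 - (1-h)³.

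For each c, h is solved so that the true value is 12% or 30%.

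**One case in full.** True 30%, c = 0.5: h = 0.1914 and q = 0.8086 × 0.5 = 0.4043. The true value is 0.1914 × (1 + 0.4043 + 0.1635) = 30.0%. 1-KM = 1 - 0.8086³ = 47.1%.

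| c per 8 weeks | 1-KM when truth is 12% | 1-KM when truth is 30% |
|---|---|---|
| 0 | 12.0% | 30.0% |
| 0.1 | 13.2% | 32.9% |
| 0.3 | 16.2% | 39.6% |
| 0.5 | 19.9% | 47.1% |
| 0.6 | 22.1% | 51.1% |
| 0.7 | 24.4% | 55.0% |

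The ratio runs from 1.1 at c = 0.1 to 1.8 (truth 30%) or 2.0 (truth 12%) at c = 0.7. With no competing events the two estimates agree.

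**Rates that vary over time (assumed).** Here the number at risk is multiplied by (1 - response - failure) after each scan.
- Responses 12/8/5%, failures 45/40/35%: truth = 0.12 + 0.43 × 0.08 + 0.2236 × 0.05 = 16.6%; 1-KM = 1 - 0.88 × 0.92 × 0.95 = 23.1%.
- Responses 6/12/12%, failures 50/50/40%: truth = 0.06 + 0.44 × 0.12 + 0.1672 × 0.12 = 13.3%; 1-KM = 1 - 0.94 × 0.88 × 0.88 = 27.2%.

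**A cohort of 29 (assumed counts).** Responses 4/3/2, progression or death 13/3/2.
- Crude proportion: 9/29 = 31.0%.
- Non-responders censored when they fail: numbers at risk 29, 12, 6; 1-KM = 1 - (25/29)(9/12)(4/6) = 56.9%.
- Non-responders kept at risk to the end of the window: numbers at risk 29, 25, 22; 1-KM = 1 - (25/29)(22/25)(20/22) = 1 - 20/29 = 31.0%.

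The last two lines use the same patients and the same estimator. Only the censoring time differs.

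**The case against.** The strongest reply is that the article never says when non-responders are censored. Kaplan-Meier must code them as censored, but keeping them at risk to the end of the assessment window is a recognised approach, gives the crude proportion, and is compatible with analysing everyone regardless of compliance. Censoring rules for a secondary endpoint are often left to the full protocol or SAP. This stands as a limit on certainty: a reader might infer that the stated method is bound to be biased, and the article does not support that. It does not remove the point, because the article fixes an estimator whose correctness for TTR depends on an unusual censoring rule that it does not state.

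Four further replies also stand:
- **Size.** Every figure above rests on assumed failure rates, and at the low end the excess is small (13.2% against 12%).
- **Median.** A reader might infer that the median TTR would be wrong in general. In the two time-varying examples 1-KM ends at 23.1% and 27.2%, so no median is reached. It passes 50% only with a true rate near 30% and heavy failure, as at c = 0.6 or above or in the 29-patient example.
- **Comparisons.** A reader might infer that the planned comparison of group D with groups A to C is distorted. Secondary objectives speaks of patient outcomes without naming TTR, and the methods plan only estimation with confidence intervals.
- **Progression.** It is not terminal for immune-related response. The text on the phase II primary outcome under Assessments and collection of outcomes provides for iRECIST or iRANO assessment in patients treated beyond progression. Counting progression as a competing event throughout would discard later responses.

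**Conclusion.** The point holds in conditional form. Under censoring at progression, death or last assessment, Kaplan-Meier in all treated patients overstates the probability of responding whenever such events occur while responses are still accruing. The direction is always upward. Over an assumed 10% to 70% failure per 8-week interval, a true 30% appears as about 33% to 55% and a true 12% as about 13% to 24%. Given competing events of that kind, the excess is avoided only if non-responders remain at risk to the end of the window, which the article does not state.

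The consequences are confined to TTR. Futility and activity rest on the binomial response rate and its posterior probabilities, and that rate is reported directly with its own interval in each cohort. Kaplan-Meier suits PFS and OS, and duration of response is already limited to responders. A reader might infer that the trial's conclusion on activity is affected; nothing in the article supports that. It is worth correcting before analysis, but it is not a flaw in the design.

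**What to change.** Replace Kaplan-Meier for TTR by the cumulative incidence of first CR or PR (Aalen-Johansen, with 95% confidence intervals) in all patients who started treatment, and state the competing events for each type of response:
- **RECIST/RANO response:** progression, new therapy and death, each without prior response.
- **Immune-related response (iRECIST/iRANO):** death, and new therapy or end of response follow-up, but not initial progression.

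Also describe TTR among responders, labelled as conditional on response. Keep Kaplan-Meier for PFS and OS.

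The change uses data already collected and alters no sample size or decision rule. It costs a sentence or two in the plan and slightly more analysis work, and the TTR curve will look less favourable than one from Kaplan-Meier with ordinary censoring.

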## Discussion

Pediatric patients with relapsed or refractory disease represent a population with a desperate need for new innovative treatment approaches. The INFORM2 NivEnt trial intends to exploit the immune enhancing effects of entinostat on nivolumab as an innovative new approach. As opposed to the commonly used “all comer” strategy in early phase trials, this trial applies a biomarker-driven approach in order to maximize the chance of detecting early signs of activity. The design allows at the one hand increasing the likelihood of identifying an activity signal by stratifying based on rational biomarkers, while on the other hand it prevents children being exposed to unnecessary risks by early stopping for futility. Early stopping for futility is also applied by other pediatric trials [47]. Large adult initiatives like the National Lung Matrix Trial started to use the Bayesian adaptive design for futility analysis [48]. The Bayesian adaptive design allows more flexibility concerning the number of interims and the final number of patients in each cohort than a frequentist approach [36, 37]. It also opens the possibility to adaptively pool evidence across all cohorts [49] and is therefore applied in the INFORM2 NivEnt trial. In addition, this strategy allows for testing of a new (combination) treatment with relatively brief trial execution timelines and thereby accelerates drug development.

Although the molecular diagnostics typically applied before enrollment [39] are not routinely available in all countries, this is currently changing rapidly in Europe where platforms like the INFORM Registry are becoming available in additional countries every year. For the primary endpoint it could be sufficient to determine only the three relevant biomarkers, but to allow exploration of further potential mechanisms behind responders and non-responders (e.g. potential new biomarkers like immune signatures and infiltration), it is important to have fully molecularly profiled tumors for all patients.

Basket protocols can be challenging due to their complexity, especially when they include adaptive designs. Protocol readability, number and oversight of amendments, sponsor trial oversight, trial governance and a high level of necessary statistical support are well known issues [50]. With four more or less similar arms regarding treatment and statistics in INFORM2 NivEnt, the level of complexity seems justified when considering the acceleration the design offers to drug development in pediatric oncology (with the Bayesian adaptive design also preventing children being exposed to unnecessary risks). By providing the web tool for analytical calculations online (http://biostatistics.dkfz.de/BDP2/), full transparency regarding the Bayesian adaptive design is guaranteed. Subsequent INFORM2 trials following the same robust design are currently in preparation, and will be submitted to the regulatory authorities under a master protocol concept as described before [50]. This will reduce the complexity for investigators, sponsor, statisticians, ethics committees and competent authorities for future INFORM2 trials. In conclusion, the INFORM2 NivEnt biomarker driven basket adaptive design provides an innovative approach accelerating drug development and reducing exposure to investigational treatments in this vulnerable patient population at the same time.

### Trial status

Protocol version: 9 January 2019, Final2Date recruitment start: 26 July 2019Estimated recruitment completion: Q3 2021Trial registration: ClinicalTrials.gov, NCT03838042. Registered on 12 February 2019.

## Data Availability

Data sharing is not applicable to this article as no datasets were generated or analyzed yet. However, future pseudonymized trial data will be shared in the context of publications and after publication with other physicians and scientists (national and international academia) to promote and accelerate research on causes and treatment development of oncological diseases.

## Abbreviations

AE: Adverse Event
ADME: Absorption, distribution, metabolism and excretion
ALT: Alanine aminotransferase
AST: Aspartate aminotransferase
CSF: Cerebrospinal fluid
CTCAE: Common Terminology Criteria for Adverse Events
eCRF: Electronic Case Report Form
DLT: Dose Limiting Toxicity
DMC: Data Monitoring Committee
DOR: Duration of response
GPOH: Society of Pediatric Oncology and Hematology
HDAC: Histone deacetylase
HDACi: HDAC-inhibitor
INFORM: INdividualized Therapy FOr Relapsed Malignancies in Childhood
iRANO: Immunotherapy RANO
iRECIST: Immune-related RECIST
ITCC: Innovative Therapies for Children with Cancer
MB: Megabase
PD-L1: Programmed Death-Ligand 1
PDX: Patient derived xenograft
RANO: Response assessment in neuro-oncology
RECIST: Response evaluation criteria in solid tumors
RPKM: Reads Per Million Rotal Reads Per Kilobase of Exon Model
RP2D: Recommended Phase 2 Dose
SNV: Single-nucleotide variant
VHP+: Voluntary Harmonisation Procedure plus
